#### Statistical analysis

Statistical analysis will be performed using the R statistical software (
http://www.r-project.org). A two-sided *P* value <0.05 will be considered significant. For baseline characteristics, descriptive statistics will be used. For analysis of the primary outcome, a Mann-Whitney *U* test will be applied. For categorical secondary endpoints, chi-square statistics will be used. To compare continuous secondary endpoints (operating time, length of hospital stay, analgesic use, time to return to normal activity), Mann-Whitney *U* tests will be applied. No interim analysis is planned for this study. For the time course of pain at provocation and at rest, a mixed model with mean VAS scores will be applied.

Missing values will be replaced with the last available value (the last observation carried forward (LOCF) approach). Data from patients who withdraw from the study will be disregarded unless exclusion is based on postoperative patient wishes and the patient agrees to the use of the already obtained data.

The confirmatory analysis will be performed based on intention-to-treat (ITT) patients and with respect to ITT principles. A standard sensitivity analysis will be performed on the per-protocol population.

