### Randomization, allocation concealment, and blinding

The SDGC will enroll and randomize patients immediately after diagnostic laparoscopy and confirmation of the technical feasibility of both procedures by the surgeon. The patients will be randomized using an online randomization tool (
http://www.randomizer.at). Randomization will be stratified by computer-generated permuted blocks of varying size with a 1:1 ratio to the experimental and control intervention groups. Patient allocation will be revealed to the surgeon after randomization by a study nurse using a written form, which will be destroyed immediately after unveiling. A standardized wound dressing will be applied after both techniques to cover the trocar and minilaparotomy sites (Figures 
2 and
3). Investigators and patients will be blinded to the group affiliation until removal of the wound dressing at discharge. The study visits will be performed by investigators who are not involved in the surgical procedures. The wound dressing will be changed with the patient blinded using blinding glasses on postoperative day (POD) 2 and at 3-day intervals thereafter. At each center, a study nurse will be in charge of changing the wound dressing and will not be involved further in the trial. If unscheduled wound dressing is necessary, the indication and time point will be documented. In the case of wound complications, patients and investigators will be unblinded. The surgical report and all patient files will be blinded for surgical technique. To evaluate the success of the blinding procedure, the patient's and investigator's suspicion of group affiliation will be documented before measuring the primary endpoint and before regular unblinding at discharge. In the case of adverse events, unblinding may be performed prematurely based on the assessment of the principal investigator. The patients' allocated interventions can be revealed at any time by accessing the allocation list within the trials office.

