### Risk-benefit ratio

The potential benefits of transvaginal hybrid NOTES sigmoid resection are expected to be less postoperative pain, faster convalescence, and reduced risk of wound infections and incisional hernia compared to conventional methods. The potential complications related to NOTES access are disturbed vaginal wound healing, impaired sexual function, and transvaginal microbiological contamination of the peritoneal cavity. In a recent study, we found a positive bacterial culture in the Douglas pouch following colpotomy in 2 of 27 (7%) patients undergoing transvaginal cholecystectomy. However, in both cases peritoneal contamination did not impact morbidity
[15]. Two studies assessed postoperative sexual function after transvaginal NOTES cholecystectomy and did not find impairment after a follow-up of 12 months
[16, 17]. In a cohort study of 44 patients undergoing transvaginal hybrid NOTES sigmoid resection we found major complications (≥grade 3) in 2 patients (4.4%) and minor complications (<grade 3) in 10 patients (22.2%)
[11]. No mortality occurred
[11]. Overall, these rates are comparable to previously published literature on assisted laparoscopic sigmoid resection for diverticular disease
[18, 19]. Consequently, no evidence yet indicates higher morbidity after transvaginal hybrid NOTES sigmoid resection compared to the assisted laparoscopic approach.

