#### Secondary endpoints

Secondary endpoints will be measured intraoperatively, at daily study visits, and 3, 12, and 36 months postoperatively. Intraoperative parameters comprise operation time, length of minilaparotomy, height of the anastomosis and the length of the unfixed specimen. The number of harvested lymph nodes will be determined postoperatively by pathological examination. The schedule for study visits and follow-up is provided in Table 
2. Pain intensity will be measured at rest and during mobilization in the same way as the primary endpoint. The dose and identity of applied analgesics will be recorded daily. Daily analgesic use will be graded using a numeric scale from one to three according to the WHO analgesic ladder
[14]. Cumulative analgesic use will be assessed by adding daily WHO analgesic ladder scores. Daily patient mobility will be measured in meters by an electronic pedometer device, which will be placed on the wrist of the nondominant hand of the patient. Cumulative patient mobility will be assessed by adding daily distances. Inflammatory parameters (leukocytes, C-reactive protein) will be measured daily from POD 1 to POD 5. The discharge criteria (See ‘Discharge criteria’) will be evaluated beginning from POD 5. After discharge, the patients will be asked to record daily analgesic use and activity on a scale ranging from 0 (inactivity) to 5 (return to usual activities) until they return to usual activities and stop pain medication on a standardized form, which will be evaluated at the 3-month follow-up visit. Morbidity according to Dindo *et al*.
[20] will be assessed at discharge, 3, 12, and 36 months postoperatively. The following patient-reported outcomes will be assessed preoperatively and 3, 12, and 36 months postoperatively: quality of life measured by the Gastrointestinal Quality of Life Index (GIQLI)
[21], sexual function measured by the Female Sexual Function Index (FSFI)
[22], and cosmetic satisfaction measured by the Body Image Scale
[23].

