### Statistical methods

#### Sample size

Sample size was determined for the primary endpoint, the intensity of pain during mobilization measured on the VAS 24 hours after surgery. Park *et al*. reported a mean (± standard deviation) VAS score of 4.2 ± 1.7 for transvaginal hybrid NOTES vs. 5.7 ± 1.7 for conventional laparoscopic right-sided hemicolectomy
[10]. According to Gallagher *et al*. a standardized effect size of unity in the VAS score (difference in unity given a standard deviation of unity) is discriminable by patients and can be considered clinically relevant
[25]. We made the following assumptions when calculating the patient number:

 Hypothesis: transvaginal hybrid NOTES sigmoid resection causes less pain than laparoscopic-assisted sigmoid resection 24 hours after surgery (superiority analysis). Two-sided analysis with a type I error (α) of 0.05 and power (1-β) of 0.90. The standardized effect size was assumed to be 1 (difference in VAS of 1 and standard deviation of 1). The power was set at 0.90 because some evidence is already available.

Based on these assumptions, a sample size of 23 patients per arm was calculated using the R package (version 0.1-8;
http://cran.r-project.org/web/packages/Sample.Size/index.html, *t* test for two independent samples). Assuming a drop-out rate of 20%, the total number of patients needed per arm is 29, resulting in a total patient number of 58 patients for the primary arm.

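### The general rule for continuous secondary outcomes is an unadjusted Mann-Whitney test, and no baseline-adjusted analysis is stated for GIQLI, FSFI or Body Image although preoperative scores are collected

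*Protocol article*

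**What the plan says.** On GIQLI, FSFI and the Body Image Scale, the protocol article (Secondary endpoints) says: "The following patient-reported outcomes will be assessed preoperatively and 3, 12, and 36 months postoperatively". Under Risk-benefit ratio it says of the experimental access: "The potential complications related to NOTES access are disturbed vaginal wound healing, impaired sexual function". FSFI is therefore the instrument for a harm that the article itself names.

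The Statistical analysis section sets these rules:

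- Baseline characteristics are described only.
- Categorical secondary outcomes get a chi-square test.
- For continuous ones: "To compare continuous secondary endpoints (operating time, length of hospital stay, analgesic use, time to return to normal activity), Mann-Whitney" U tests.
- A mixed model is given for the time course of pain.
- Missing values are filled by LOCF, with no restriction to particular outcomes.

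The three questionnaires are not mentioned in that section, either in the bracket or elsewhere.

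**The concern.** The bracket can be read in two ways. If it gives examples, the three scores fall under a test that makes no use of the preoperative value or of the repeated visits. If it is a complete list, the section states no analysis for them. Examples is the more natural reading: patient mobility, CRP and leukocytes are also continuous secondary outcomes outside the bracket, and a complete list would leave them without a test too.

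On either reading, the text does not commit to using a baseline that the trial already collects. This matters most for FSFI. The trial is sized for pain at 24 hours, so the comparison of sexual function will be imprecise. A test that returns only a P value does not show how large an impairment remains compatible with the data. LOCF adds a second problem: for a patient with no follow-up questionnaire, the last available value is the preoperative one, and carrying it forward records no change on a question about harm.

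**Working it through.** **Inputs from the article.** From the Sample size section under Statistical methods: α 0.05 on two sides, target power 0.90, a VAS difference of 1 with SD 1, and 23 evaluable patients in each arm before allowing for losses. The allowance for losses reads: "Assuming a drop-out rate of 20%, the total number of patients needed per arm is 29". From the Randomization section: equal allocation to the two arms.

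**Assumed inputs.** The correlation r between preoperative and follow-up score is not in the article; 0.3, 0.5 and 0.7 are used. Results are in SD units of the follow-up score, because no SD is given for these scores. A 0.5 SD arm difference serves as illustration only.

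**The plan's own figure.** For a two-sample t test with standardized effect 1 and two-sided α of 0.05, the noncentral t distribution gives power 0.8997 with 22 per arm and 0.9125 with 23. So 23 is correct. Inflation gives 23 / (1 − 0.20) = 28.75, that is 29 per arm and 58 in total. The stated figures reproduce.

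**Gain from baseline adjustment.** With n = 23 evaluable per arm:

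- Variance factor: 1 − r².
- Equivalent unadjusted patients per arm: 23 / (1 − r²).
- 95% CI half-width: 1.960 × √(2/23) × √(1 − r²).
- Difference detectable with 80% power: (1.960 + 0.842) × √(2/23) × √(1 − r²).

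| Analysis | 1 − r² | Equivalent n per arm | CI half-width (SD) | Detectable difference (SD) |
|---|---|---|---|---|
| Unadjusted means | 1 | 23 | 0.58 | 0.83 |
| Adjusted, r = 0.3 | 0.91 | 25.3 | 0.55 | 0.79 |
| Adjusted, r = 0.5 | 0.75 | 30.7 | 0.50 | 0.72 |
| Adjusted, r = 0.7 | 0.51 | 45.1 | 0.41 | 0.59 |

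These are normal approximations. For Mann-Whitney with normal data, the detectable difference is 0.83 / √(3/π), about 0.85 SD.

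**Simulation.** Normal data, 4,000 runs per setting, true difference 0.5 SD, 23 per arm. Power of Mann-Whitney on the follow-up score against ANCOVA was 36% against 40% (r = 0.3), 35% against 47% (r = 0.5) and 36% against 63% (r = 0.7). With no true difference, both tests rejected in roughly 5% of runs.

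**LOCF.** Let a share p of each arm have only a preoperative score, for reasons unrelated to outcome. Randomization makes the expected arm difference in carried-forward values zero, so the expected mean difference becomes (1 − p) × Δ. If p were 0.20, borrowing the drop-out rate only as an illustration, a true difference Δ would appear as 0.80 × Δ.

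**The case against.** The strongest reply is that the quoted sentence does not name these scores, and that none of the four outcomes it lists has a preoperative score. A reader might infer that the plan discards the preoperative scores, or that Mann-Whitney is its only method and is run visit by visit. The article says none of this. It does not rule out a Mann-Whitney test on change from baseline, it gives pain a mixed model, and it condenses a full protocol that may say more. Those stronger readings fall.

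It is also true that an unadjusted test is valid in a randomized trial, because its type I error already allows for chance imbalance. One might infer that such imbalance could match the effect sought, but no effect is stated for these scores. Working from 29 per arm would ignore the planned 20% drop-out. At r = 0.3 the gain is slight, and even at r = 0.5 the interval extends 0.50 SD either side of the estimate, so adjustment does not make the trial large enough to settle the question of harm.

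On LOCF, the article plans to complete missing follow-up by phone and to disregard most data from patients who withdraw. Both limit how often a preoperative score would be carried forward, but the rule as worded does not prevent it.

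What remains is that the one general rule in the text, followed as written, gives a less precise comparison than the collected data allow.

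**Conclusion.** The point holds as an avoidable loss of precision on secondary outcomes, one of which addresses a named harm. It is not an error that invalidates a comparison. At 23 evaluable patients per arm, adjustment is worth about 2, 8 or 22 further patients per arm for r = 0.3, 0.5 or 0.7. The size rests entirely on the assumed r and cannot be fixed from the article; the direction does not depend on it. The LOCF effect pulls the arms together when patients lack any follow-up score, and its size depends on a share that the article does not give for these questionnaires. The primary analysis and the sample size of 58 are unaffected.

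**What to change.** In the Statistical analysis section, name the analysis of GIQLI, FSFI and the Body Image Scale:

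- Include the preoperative score as a covariate, either by ANCOVA at each visit or by a repeated-measures mixed model on the observed follow-up values.
- If the mixed model is used, say that it replaces LOCF for these three scores. If ANCOVA is used, say that a preoperative score is not carried forward as a follow-up value.
- Report the adjusted arm difference with its 95% CI at 3, 12 and 36 months.
- State that FSFI is interpreted from the confidence interval, and that a non-significant P value is not taken as evidence of no harm.

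If the full protocol or analysis plan already contains this, a cross-reference is enough. The cost is analysis wording only: no new data, visits or patients are needed.

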### Perioperative management, discharge, and follow-up

Perioperative thrombosis prophylaxis will be performed according to current German guidelines
[13]. Single-shot antibiotics (ampicillin/sulbactam) will be given 30 minutes before surgery. Intraoperative anesthesia will comprise intravenous administration of piritramide. Postoperatively, pain medication will be administered according to the World Health Organization (WHO) analgesic ladder based on the judgment of the treating ward physician beginning directly after surgery in the recovery room
[14]. Nonsteroidal anti-inflammatory drugs (metamizol) will be administered solely or in combination with a weak (tilidine) or strong opioid (piritramide, oxycodone). Peridural analgesia is not part of the pain management in this study. On the day of surgery and POD 1, analgesics will be administered intravenously. Beginning from POD 2, analgesics will be applied orally in cases of tolerated oral intake. Daily blood samples are scheduled for POD 1 to 5. Patients will be encouraged for discharge from POD 5 onward upon complete fulfillment of the discharge criteria (see ‘Discharge criteria’). Patients who receive the experimental intervention will be recommended to attend an ambulatory gynecological checkup 10 days after surgery. All patients will be followed up at an ambulatory checkup scheduled 3, 12, and 36 months after surgery. The ambulatory checkup will comprise taking a history, a clinical examination, and an assessment of secondary endpoints. Patients will be notified in writing and by phone in case they fail to return for their follow-up visits. If reaching the patients directly is not possible, their general practitioner will be contacted. Missing follow-up data will then be completed by phone.

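### Time to return to normal activity is a right-censored time, but the plan gives it a Mann-Whitney test and blanket last-observation-carried-forward, which yields no valid value for a patient not seen to recover

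*Protocol article*

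**What the plan says.** All references are to the protocol article.

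- **Test** (Statistical analysis): the rank test is assigned in the words "To compare continuous secondary endpoints (operating time, length of hospital stay, analgesic use, time to return to normal activity), Mann-Whitney".
- **Missing data** (same section): "Missing values will be replaced with the last available value". The rule is general; no endpoint is exempted.
- **Withdrawals** (same section): "Data from patients who withdraw from the study will be disregarded unless exclusion is based on postoperative patient wishes". The exception also needs her consent to keep what was collected up to then.
- **How the endpoint arises** (Secondary endpoints): after discharge patients "record daily analgesic use and activity on a scale ranging from 0 (inactivity) to 5 (return to usual activities"). They continue "until they return to usual activities and stop pain medication on a standardized form, which will be evaluated at the 3-month follow-up visit". Table 2 marks this endpoint at the 3-month visit only.
- **Recovery of missing data** (Perioperative management, discharge, and follow-up): after written, telephone and general-practitioner contact, "Missing follow-up data will then be completed by phone".

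The article states no censoring rule. It also gives no value for a patient who is unrecovered at 3 months or whose form stops earlier.

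**The concern.** The time is observed only if the patient reaches the top activity score while still completing the form. Otherwise all that is known is that recovery took longer than the last completed day. The plan treats this as an ordinary continuous value and sends any gap to a rule made for repeated measurements.

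Faster convalescence is one of the expected benefits of the experimental procedure (Abstract, Rationale, Risk-benefit ratio), and the Discussion names this endpoint among the recovery outcomes. Slow recoverers have more days on which to abandon the form, so incompleteness is tied to the outcome. Blinding ends at discharge, when the home diary starts, so completion could differ by arm. The stakes are lost power, and bias if completion does differ.

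**Working it through.** **1. The plan's own figure.** The article sizes the trial for pain only, with "Two-sided analysis with a type I error (α) of 0.05 and power (1-β) of 0.90" and a standardized difference of 1. Normal approximation: 2 × (1.960 + 1.282)² / 1² = 21.02, so 22 per arm. The exact two-sample t test needs 22.02, so 23 (power 0.912). With 20% drop-out, 23 / 0.80 = 28.75, so 29 per arm and 58 in total. The stated figures reproduce. They are used here only for n = 29 per arm.

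**2. What LOCF can mean here.** Take a form that stops on day 20 at a score below 5.
- Carry the *score* forward: the patient never reaches 5, no time exists, and she leaves the Mann-Whitney test.
- Use the *last diary day* as the time: she enters as recovered on day 20, which did not happen.

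The article does not say which is meant. Neither gives a valid time.

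**3. Size.** The article gives no recovery times or completion rates, so every input below is an assumption: 29 per arm, form read at day 90, early stop on a random day unrelated to the patient's own recovery time. Settings were simulated with 1,500 to 2,000 trials where the number is recorded. Log-normal times have sigma 0.6. Early stops are given as experimental / control.

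Power:

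| Times; medians (days); stop window | Early stops | Mann-Whitney, last day | Mann-Whitney, dropped | Log-rank |
|---|---|---|---|---|
| Exponential; 20 vs 40 | none | about 0.60 | – | 0.69 |
| Exponential; 20 vs 40; days 7–40 | 20% / 20% | 0.48 | 0.23 | 0.65 |
| Exponential; 20 vs 40; days 7–40 | 10% / 30% | 0.29 | 0.12 | 0.64 |
| Log-normal; 25 vs 40 | none | 0.81 | 0.73 | 0.76 |
| Log-normal; 25 vs 40; days 5–90 | 20% / 20% | 0.76 | 0.68 | 0.75 |
| Log-normal; 25 vs 40; days 5–90 | 40% / 40% | 0.66 | 0.62 | 0.73 |
| Log-normal; 25 vs 40; days 5–90 | 10% / 30% | 0.63 | 0.61 | 0.75 |
| Log-normal; 25 vs 40; days 7–40 | 10% / 30% | 0.41 | 0.57 | 0.75 |
| Log-normal; 20 vs 40; days 7–40 | 20% / 20% | 0.95 | – | 0.975 |
| Log-normal; 20 vs 40; days 7–40 | 10% / 30% | 0.84 | 0.90 | 0.96 |

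Reading the table:
- Exponential, 20% stops: the gap to log-rank is 0.65 − 0.48 = 0.17. With no early stops it is already 0.69 − 0.60 = 0.09. About half (0.09 / 0.17 = 0.53) therefore comes from the choice of test under proportional hazards.
- In that setting the control median reads 31.9 days instead of 40 if the last day is used.
- Dropping costs so much with exponential times because 0.5^(90/40) = 21% of controls but only 0.5^(90/20) = 4% of experimental patients are unrecovered at day 90.
- Log-normal, 25 vs 40, 20% stops (days 5–90): the mean difference in medians shrinks from 15.1 to 13.6 days (last day) or 12.3 days (dropped).

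Type I error, equal medians:

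| Times; median (days); stop window | Early stops | Last day | Dropped | Log-rank |
|---|---|---|---|---|
| Log-normal; 35; days 5–90 | 20% / 20% | 4.7% | 4.6% | 5.1% |
| Log-normal; 35; days 5–90 | 10% / 30% | 5.8% | 5.3% | 5.7% |
| Log-normal; 35; days 5–90 | 10% / 60% | 14.5% | 7.7% | 5.9% |
| Exponential; 30; days 7–40 | 10% vs 30% | 6.4% | – | 4.6% |
| Log-normal; 30; days 7–40 | 10% vs 30% | 8.9% | – | 6.0% |

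Simulation error at 5% is √(0.05 × 0.95 / 1500) = 0.56 points for the first three rows and √(0.05 × 0.95 / 2000) = 0.49 for the last two. So 5.8% cannot be told from 5%, while 8.9% and 14.5% can. A separate log-normal run at 10% vs 30% gave 9.2% (last day) against 5.6% (log-rank).

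**4. Would worst ranks under Mann-Whitney suffice?** If the only incompleteness is the common 3-month reading, yes: log-normal type I error is 4.9%, and power is 0.81 against 0.76 for log-rank. If early stoppers also take the worst rank and stopping is 10% vs 30%, type I error is 6.4% (exponential) or 9.3% (log-normal), no better than using the last day.

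**The case against.** A reader might infer that the plan counts incomplete diaries as early recoveries. It does not say so. The recorded value is a daily score, and carrying forward a score below 5 gives a patient who has not recovered. Using the last diary day as the time is only one possible application.

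A reader might also infer that the diary ends at 3 months. It runs until recovery; 3 months is when it is evaluated, and Table 2 schedules no later reading.

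Further points on the other side:
- **Telephone completion** should shrink the gap. This stands in part. The provision is framed around missed visits, and a date from a daily diary is hard to recover by recall.
- **Mann-Whitney is not wrong in itself.** This stands for a common 3-month cut-off with tied worst ranks. The article states no such rule, and the rule does not cover forms that stop early in unequal proportions.
- **The power loss is overstated if log-rank is the yardstick.** This stands for exponential times, hence the no-early-stop rows. With log-normal times and equal 20% stopping the difference from log-rank is negligible (0.76 vs 0.75; 0.95 vs 0.975).
- **Log-rank assumes non-informative censoring**, which sits badly with the argument that slow recoverers stop their forms. This stands. The simulations favour log-rank because stopping there does not depend on recovery time.
- **A condensed article may leave such detail to the full protocol or analysis plan.** This would answer a complaint about silence. Here the article itself fixes the test and a general imputation rule, and the two do not fit this endpoint.

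**Conclusion.** The concern holds in limited form. The plan fixes Mann-Whitney and blanket LOCF for a right-censored time, and neither way of applying LOCF gives a valid value for a patient not observed to recover.

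The size rests on assumed recovery times and completion rates. With about equal stopping in both arms, type I error stays near 5% and the effect is lost power. The loss is slight to moderate if the last diary day is used: 0.81 to 0.76 (log-normal, 25 vs 40 days) and about 0.60 to 0.48 (exponential), at 20% stops. It is larger with exponential times if such patients are dropped (0.23). Bias needs completion to differ by arm. At 10% vs 30%, type I error with the last day ranged from 5.8% to 9.2%, depending on the distribution and when forms stop. Nothing in the article shows that completion will differ; the end of blinding at discharge only makes it possible.

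This is one secondary endpoint. The pain analysis and the 58-patient sample size are untouched, so the point is minor.

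**What to change.** In the Statistical analysis section:

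1. Take time to return to normal activity out of the Mann-Whitney list and exempt it from LOCF.
2. Analyse it by Kaplan-Meier curves and a log-rank test. Censor patients without return at their last completed diary day, at the latest the 3-month visit.
3. Because censoring may be informative, add a sensitivity analysis that gives unrecovered patients the worst rank. Report it as a check in the opposite direction, since it does not repair unequal stopping. Show the number of incomplete forms by arm beside it.

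The cost is two or three sentences. No new patients, visits or data are needed, because the daily form already carries the days. Recruitment had not begun at the time of the article, so the change can be made before any data exist. The remaining weakness is the non-informative censoring assumption, which step 3 makes visible but does not remove.

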### Outcome parameters

#### Primary endpoint

The primary endpoint is intensity of pain measured by a visual analogue scale (VAS) during mobilization of the patient 24 hours postoperatively. Patients and investigators will be blinded for this measurement. Before mobilization of the patient, the investigator will provide a standardized explanation of the VAS using a written text. The patient will be asked to record current pain intensity by drawing a vertical line on a horizontally positioned 100-mm VAS ranging from 0 (no pain) to 10 (worst imaginable pain). For mobilization, patients will be asked to take a seated position at the edge of the bed, to stand up, and finally to lie down in bed again. Immediately after mobilization, the patient will be asked to record the maximum pain intensity experienced during mobilization.

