**Table 2 Tab2:** **Postoperative outcome parameters and schedule of study visits and follow-up**

Outcome parameter	Daily in-hospital study visits				Follow-up		
	POD 1 (24h) ^*^	POD 2 to POD 5	≥ POD6	Discharge	3 months	12 months	36 months
Pain intensity (VAS)	X (primary outcome)	X	X	X			
Daily analgesic use	X	X					
Cumulative analgesic use		X (POD 5)^†^		X	X		
Daily patient mobility	X	X		X			
Cumulative patient mobility				X			
Inflammatory parameters (CRP, leukocytes)	X	X					
Discharge criteria		X (POD5)^†^	X				
Length of stay				X			
Morbidity				X	X	X	X
Return to normal activities					X		
Quality of life (GIQLI [21])					X	X	X
Sexual function (FSFI [22])					X	X	X
Cosmetic satisfaction (Body Image Scale [23])					X	X	X

^*^Study visit on POD 1 is scheduled 24 hours postoperatively; ^†^parameters will be measured solely on POD 5. CRP, C-reactive protein; FSFI, Female Sexual Function Index; GIQLI, Gastrointestinal Quality Of Life Index; POD, postoperative day; VAS, visual analogue scale.

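### LOCF for every missing value gives the 24-hour mobilization VAS either a resting score or no value at all, and enters preoperative questionnaire scores as postoperative outcomes

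*Protocol article*

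**What the plan says.** The missing-data rule in the Statistical analysis section is one sentence: "Missing values will be replaced with the last available value (the last observation carried forward (LOCF) approach". It names no endpoint. The same section makes the intention-to-treat analysis confirmatory, so the rule reaches the primary Mann-Whitney test. The only sensitivity analysis listed is per-protocol. Data from patients who withdraw are mostly disregarded.

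The Primary endpoint section defines a single measurement: "The primary endpoint is intensity of pain measured by a visual analogue scale (VAS) during mobilization of the patient 24 hours postoperatively". Two marks are made at that visit. Before getting up: "The patient will be asked to record current pain intensity by drawing a vertical line on a horizontally positioned 100-mm VAS". Afterwards: "Immediately after mobilization, the patient will be asked to record the maximum pain intensity experienced during mobilization". The second mark is the endpoint. The Secondary endpoints section keeps the two measures apart: "Pain intensity will be measured at rest and during mobilization in the same way as the primary endpoint". The footnote to Table 2 fixes the time, "Study visit on POD 1 is scheduled 24 hours postoperatively", and the table shows no pain score before that visit.

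For quality of life, sexual function and cosmetic satisfaction, the Secondary endpoints section says "The following patient-reported outcomes will be assessed preoperatively and 3, 12, and 36 months postoperatively". For the course of pain over time, the analysis section plans a mixed model.

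**The concern.** LOCF needs an earlier value of the same quantity. The primary endpoint has none in the schedule. A patient who marks her resting pain and then cannot or does not complete the mobilization could be scored at rest. The Discussion explains that pain during mobilization was chosen because mobilization may provoke pain even under closely monitored analgesia, so the substitute is the measure that the trial decided not to use. If such patients are unevenly spread between the arms, the confirmatory comparison tilts toward the arm with more of them.

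For the questionnaires, the last value before a missing 3-month score was recorded before surgery. Entering it as an outcome states that nothing changed. This matters most for the FSFI, because the Risk-benefit ratio section names impaired sexual function among the potential complications of the transvaginal access.

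For the daily pain course, LOCF adds invented readings, treated as observed, to a mixed model that can use incomplete series as they stand.

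**Working it through.** **1. What LOCF can supply for a missing primary value**

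| Situation at 24 hours | Earlier VAS in the schedule | Result of the rule |
|---|---|---|
| Resting mark made, no mark after mobilization; last available value taken literally | Resting score, same visit | Resting score analysed as mobilization pain |
| Same, but LOCF kept within the mobilization variable | None | Undefined |
| Whole visit missed | None | Undefined |

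No row gives a valid value.

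**2. Questionnaires.** The measurement times are preoperative, 3, 12 and 36 months. If 3 months is missing, the preoperative score is carried forward, and it also fills 12 and 36 months if those are missing. If 3 months was observed, that score is carried instead.

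**3. The plan's own sample size.** Inputs from the Sample size section: difference 1, SD 1, two-sided α 0.05, power 0.90, drop-out 20%. The two-sample t test gives n = 22.02, rounded up to 23 per arm. Then 23 / 0.8 = 28.75, rounded up to 29 per arm, 58 in total. The plan's figure is reproduced, and nothing below changes it. The drop-out allowance is 0.2 × 29 = 5.8, about 6 per arm.

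**4. Size of the effect if the resting score is used.** The documents do not give the gap between resting and mobilization pain. Assumed: SD 1, resting pain 1, 2 or 3 points lower, correlation 0.5 between the two marks, 29 per arm, values missing at random within arm.

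Shift in the mean difference, toward the arm with more missing values = (difference in missing counts) × gap / 29:
- 6 vs 0: 6/29 = 0.21; 12/29 = 0.41; 18/29 = 0.62
- 6 vs 2: 4/29 = 0.14; 8/29 = 0.28; 12/29 = 0.41
- 3 vs 2: 1/29 = 0.03; 2/29 = 0.07; 3/29 = 0.10

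Simulated Mann-Whitney test (at least 10,000 runs per setting):

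| Setting | Gap 1 | Gap 2 | Gap 3 | Missing values omitted |
|---|---|---|---|---|
| Type I error, 6 vs 0 | 0.10 | 0.17–0.18 | 0.22 | 0.05 |
| Type I error, 6 vs 2 | 0.06 | 0.08 | 0.09 | 0.05 |
| Type I error, 3 vs 2 | 0.04 | 0.04 | 0.03 | 0.05 |
| Type I error, 6 vs 6 | 0.03 | 0.02 | 0.01 | 0.04 |
| Power, true difference 1, 6 vs 6 | 0.94 | 0.87 | 0.78 | 0.90 |
| Power, true difference 1, 6 missing in control arm only | 0.80 | 0.52 | 0.30 | 0.93 |

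With complete data the power is 0.95. When missing counts are equal or nearly so, type I error is not inflated. At gaps of 2 to 3 points, power with six missing per arm falls below that from simply leaving the missing values out.

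**The case against.** LOCF normally carries a value forward within one variable, and the plan treats rest and mobilization as separate variables. On that reading the resting score never enters the primary analysis, and the rule is undefined, not biased. This stands as a limit: a reader might infer that the plan definitely puts resting scores into the primary analysis, but the text does not say so. It does not rescue the rule, because an undefined rule also leaves the confirmatory analysis without a value.

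The large type I errors need about six missing values in one arm and none in the other. Six is the whole drop-out allowance spent on one inpatient visit a day after surgery, and most withdrawals never reach LOCF. This also stands: large inflation is possible but is not the expected case.

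The section on perioperative management and follow-up provides written and phone reminders, contact with the general practitioner, and completion of missing follow-up data by phone. That lowers the number of missing questionnaires. It does not change what happens to those still missing.

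Two further inferences are not supported. One is that LOCF distorts pain readings after discharge: Table 2 schedules no VAS after discharge, and discharge is possible only from POD 5. The other is that "a mixed model with mean VAS scores will be applied" means modelling averages instead of each patient's readings: it may only be condensed wording for comparing means.

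**Conclusion.** The point holds. The plan states a rule, so this is not detail left to another document, and the rule gives no valid value for a missing primary endpoint on any reading. It also allows preoperative GIQLI, FSFI and Body Image Scale scores to count as postoperative results when the 3-month score is missing.

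The size is conditional. It rests on the resting score being used, on an assumed gap of 1 to 3 points at SD 1, and on values missing at random within arm. The shift is 0.2 to 0.6 points and type I error about 9–22% at six missing against none; about 6–9% at six against two; no inflation at three against two. The shift should be read against the trial's planning difference of 1 point with SD 1. The 1.5-point difference with SD 1.7 is the result of the cited study of right-sided hemicolectomy and is not this trial's assumption.

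A reader might also infer that the FSFI comparison between arms shrinks by exactly the share of patients imputed. The article states no change-from-baseline analysis for the questionnaires. The pull toward no change is clear within an arm; between arms it depends on how the missing scores are distributed.

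**What to change.** Delete the LOCF sentence and replace it as follows.

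- **Primary endpoint.** Do not substitute the resting score. Handle a missing 24-hour mobilization VAS by multiple imputation, with arm, resting VAS and later mobilization VAS as predictors. Record why the value is missing. Add sensitivity analyses for non-random missingness: a tipping-point analysis, and worst rank for patients unable to mobilize because of pain. Worst rank should stay a sensitivity analysis: it turns the endpoint into a composite of pain and immobility, and when applied to six values in one arm that were missing for reasons unrelated to pain, it gave a simulated type I error of about 21–24%.
- **Daily VAS, GIQLI, FSFI and Body Image Scale.** Fit a mixed model to observed postoperative values without imputation. For the questionnaires, use the preoperative score as a covariate and never as an outcome.

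The cost is a little more analysis work and one CRF field for the reason. No extra patients are needed: with six primary values per arm simply omitted at random, simulated power is still about 0.90. The change is best made before recruitment begins.
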